### 2.9. Data Analysis

#### 2.9.1. Implementation Outcomes

We will use descriptive statistics for quantitative data for each of the constructs outlined and report these using means, proportions, standard deviations, or median and interquartile ranges, depending on the distribution of data. This will provide an objective measure of the implementation of the RECOVER model of care. Qualitative data from interviews or free-text comments will be analysed using thematic analysis supported by NVivo software v15 [38]. Patterns will be sought regarding perceived information and support needs, acceptability, satisfaction, information and educational needs, and barriers and enablers. Codes will be assigned to recurring themes. Consistencies and patterns in the themes will be identified and discussed with the research team and consumer advocates to achieve a consensus on findings. Findings from the formative work undertaken through these processes will be used to iteratively develop, design, and guide implementation strategies using expert recommendations for implementing change [39]. Fixed and variable costs of the model of care will be calculated to provide estimates of the resources required to sustain the model of care.

#### 2.9.2. Effectiveness Outcome Analysis

Quantitative analysis will involve collating and compiling data from various sources into the study database. Summary scores for measures at each time point will be calculated. Appropriate parametric or non-parametric tests will be used to compare the changes in outcomes between RECOVER participants and the historical control group from a previous study (*n* = 100) study, where participants will be matched as closely as possible for child age and cancer type. If possible, regression analysis will be completed to control for confounding variables.

Parent/carer knowledge, skills, and confidence will be assessed by analysing the survey responses with appropriate parametric or non-parametric tests depending on the data distribution. Data will be analysed using the IBM 28.0 SPSS programme.

#### 2.9.3. Ethical Considerations

Participation in all phases of this study is voluntary. Participants will be informed that participation will not affect their healthcare or professional relationships. If a participant is under 18, consent will be obtained from their parent/guardian. Written consent will be obtained at recruitment for all study phases. Participants will be informed they can withdraw from the study at any time, and their data will be deleted upon their request.

## 3. Discussion

Compelling data from large population-based studies highlight that childhood cancer survivors are a medically vulnerable population warranting survivorship services to optimise outcomes beyond cure [40]. However, translating the knowledge into clinical care is yet to be realised in many health services. Models of care after cancer treatment in childhood often focus on medical surveillance for cancer, neglecting the broader health and wellness needs of young survivors [3]. Moreover, many survivorship programmes do not commence until two to five years after cancer treatment, missing the opportunity to proactively address the needs of this medically vulnerable population [41]. The transition from acute treatment to survivorship care is often fragmented and fraught with difficulties as healthcare systems remain focused on the immediate needs of new cancer cases. This results in gaps in the provision of comprehensive post-treatment care. Parents of children are also calling for improvements; our earlier research identified that parents remain at an elevated risk for anxiety, depression, and symptoms associated with post-traumatic stress disorder [11]. Addressing information and support needs could mitigate this distress while also empowering parents with the knowledge they need to actively and confidently manage their child’s healthcare needs after treatment.

We aim to address these issues with the RECOVER model of care, which we will evaluate using a hybrid implementation effectiveness study. We have outlined the co-design, implementation and evaluation plans of RECOVER, which introduces a nurse-led programme of health and needs assessment, actions and resources to bridge the divide between cancer treatment and long-term survivorship. In doing so, we have addressed a significant deficit in the extant healthcare landscape for childhood cancer survivors [13].

### 3.1. Co-Design and Implementation

We described the process of co-designing the model with consumers and healthcare professionals using a human-centred approach and implementation science to maximise the potential success of the model in a real-world setting. The human-centred co-design approach embedded in the RECOVER model of care ensures that the needs of parents and children at the end of cancer treatment are central whilst simultaneously considering the constraints and resources available within the healthcare setting. The process of co-design and refinement of the model uncovered hidden assumptions, duplication of efforts, and unforeseen barriers. Identifying these was crucial to ensure that the final model could merge steps with existing processes and avoid creating unnecessary new steps.

### 3.2. Evaluation Plans

Our evaluation plans will assess implementation outcomes including the costs of sustaining the model beyond the life of the project. Using qualitative and quantitative research methods, we outlined our approach for assessing the impact and value of the project. Anticipated outcomes include the establishment of a comprehensive model for end-of-treatment care to effectively address the diverse needs of parents and children after cancer treatment.

### 3.3. Implications for Clinical Practice

The RECOVER model of care has considerable implications for clinical practice. Nurses and other healthcare professionals play a crucial role in this model, from conducting health assessments to coordinating care plans. The model emphasises the importance of continuous monitoring and management of treatment-related effects, which can lead to improved health outcomes and enhanced quality of life for survivors. Integrating this model into clinical practice can also improve communication and coordination among healthcare providers, patients, and families, fostering re-engagement with primary care providers and leading to a more patient-centred approach to care. Implementing these alternative models on a broader scale will require adequate support from non-oncologist care providers and endorsement by cancer teams and their patients [42].

### 3.4. Strengths and Limitations of This Study

One of the strengths of the RECOVER model of care is its comprehensive, multi-phase approach integrating feedback from a diverse group of stakeholders. The involvement of both consumers (parents and families) and healthcare professionals in co-design ensures the model is tailored to the real-world needs and constraints of its users. Further, by implementing science principles, this study maximises the potential for success in real-world application and sustainability.

Our study also has limitations. First, its potential bias is introduced by the voluntary participation of both parents and health professionals whose decision to participate may be influenced by their interest or personal commitment to the project, possibly affecting the generalisability of the findings. Additionally, this study relies heavily on self-reported data from surveys and interviews, which may be subject to recall bias or social desirability bias, potentially impacting the accuracy of the reported outcomes. Finally, this study’s implementation and evaluation phases are context-specific to Queensland, Australia, which may limit the applicability of the findings to other regions or healthcare systems with different resources, cultural contexts, or healthcare practises.

## 4. Conclusions

As the population of childhood cancer survivors continues to grow, it is imperative healthcare systems evolve to meet their ongoing needs. This protocol outlines the co-design of a model of care for children at the end of their cancer treatment, incorporating actions of patient/parent-reported outcomes. The objective is to integrate health and information needs within a collaborative service paradigm to assess and respond to these needs comprehensively and systematically. The model has the potential to re-establish relationships with primary care and facilitate the early detection, referral, and management of treatment-related effects among childhood cancer survivors. The model of care will be tested in a hybrid implementation effectiveness study, assessing feasibility, acceptability, effectiveness, and costs.

## Figures and Tables

**Figure 1 healthcare-13-00454-f001:**
[figure not shown]
Action research diagram [20].

**Figure 2 healthcare-13-00454-f002:**
[figure not shown]
RECOVER end-of-treatment model of care.

**Table 2 healthcare-13-00454-t002:** Issues and Implications for the RECOVER model of care.

Issue	Implication
Multi-disciplinary Team (MDT) involvement and communication needs	
The need for seamless collaboration was identified. Doubts about the feasibility of involving all team members and how this might impact the quality of care. “How can this actually happen; what is feasible in the real world?”	Concern about practical implementation, with some suggestions that a virtual MDT could work if organised properly. Although coordination between team members is needed, logistical challenges may hinder this
Communication challenges between healthcare providers and families	
Recurring concerns were voiced regarding the effectiveness of communication between healthcare providers, particularly regarding updating families and GPs on treatment and care plans. This is crucial in rural and regional settings.	Highlights the difficulties of relaying information effectively and the need for more structured, reliable methods of communication.
The role of allied health in survivorship care	
Several clinicians highlighted the underutilisation of allied health, such as pharmacists in the care team. There is a strong call for their greater involvement, especially in managing long-term side effects to improve survivorship care.	The expertise and knowledge of allied health staff are an underused resource that could fill a critical gap in care, particularly for managing long-term issues.
Resource limitations and gaps in support services	
Need for resources and staffing, especially in areas such as pharmacy, psychosocial support, and survivorship planning. Discussions about gaps in staffing and service availability negatively impact families. “Families would really benefit from a check-in at 12 and 24 months—life doesn’t always get easier.”	Although there is enthusiasm and willingness to support families, the lack of funding and resources creates substantial barriers to offering holistic care.
Family needs and psychosocial support	
Families’ psychosocial needs, including support for siblings and mental health, are crucial but often unmet. Families express a need for ongoing psychosocial support, particularly as the child reintegrates into normal life.	These discussions highlighted that while clinical treatment is paramount, emotional and psychological support for families should not be overlooked.
Survivorship care planning	
Ongoing challenges in how survivorship is managed, both in terms of the terminology used and the timing of the provision of care plans and follow-up services. Recognition there is a ‘grey area’ following the end of treatment. Families have voiced it would have been helpful to have had the connection to services without a large gap in continuity of care.	This reflects the uncertainty families experience in transitioning from active treatment to survivorship care, emphasising the need for a more structured, continuous approach to post-treatment planning.

**Table 3 healthcare-13-00454-t003:** Inclusion and exclusion criteria of the study.

Participants	Inclusion Criteria	Exclusion Criteria
Parents/carers of children treated for cancer	Child Any diagnosis of cancer; Aged 0–18 years at the time of diagnosis; Beginning surveillance or nearing the end of planned treatment or within two years of completion of treatment. Parent/carer Over 18 years; Able to read and understand English; Willing to freely provide informed consent and participate in study procedures;	Child/parents/carers deemed not suitable by clinical teams. Child with uncertain prognosis or palliative care needs.
Health professionals	Clinicians (doctors, nurses, and allied health professionals) who provide care through Queensland Health public hospitals; The participants’ nominated family general practitioner.	None; all clinicians who meet the inclusion criteria are eligible to participate.

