Participants and setting: Participants included both healthcare providers and consumers. We aimed to use snowballing techniques to recruit approximately 20 stakeholders, including young cancer survivors, parents of young cancer patients and healthcare providers. Healthcare providers were selected based on their involvement in patient care and ability to provide valuable insights. They were recruited from the Queensland Children’s Hospital and included representation across medical, nursing and allied health specialists. Consumer participants were recruited through childhood cancer parent support groups and email contacts of the Queensland Collaborative for Cancer Survivorship. We exceeded our recruitment aim as outlined in Table 1.

Procedures: The development of the RECOVER model of care followed a systematic and iterative approach guided by action research principles [20]. We conducted a series of workshops and focus groups (Figure 1) incorporating iterative cycles of planning, acting, observing and reflecting to identify and refine the processes required to deliver the essential elements of survivorship care. Discussions focused on the design of the model of care and the development of electronic resources to support the model. Stakeholders’ feedback was continuously reviewed, reflected upon, and incorporated to ensure the final model was acceptable and appropriate for consumers and healthcare providers [20].

**Table 1 healthcare-13-00454-t001:** Participant characteristics.

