**Healthcare Professionals *n* = 22**
Discipline
Nursing, *n* = 10; Includes oncology liaison nurses, neuro-surgical consultants, adolescent and young adult consultants, and regional case managers.
Allied Health, *n* = 8; Includes occupational therapy, pharmacy, speech pathology, psychology, neuropsychology, and ophthalmology.
Medical, *n* = 4; Includes paediatric oncologists, endocrinologists, and ophthalmologists, as well as general practitioners

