### 2.5. Procedures

Recruitment of parents of children with cancer: After active treatment, childhood cancer survivors will be stratified by clinical staff for risk of long-term and late effects according to validated protocols [26], identifying those who would benefit from early intervention and proactive management of the RECOVER model of care. While this process aims to identify those who would benefit most from the intervention, eligibility is broad, as outlined below, and children at lower risk are eligible if deemed clinically appropriate. As the model of care focuses on the transition from acute care services to community-based services, it is not suitable for children with uncertain prognosis, palliative care needs or other complexities. For these reasons, clinical staff review the suitability of all participants. Details of the parents of eligible children will be passed to the research nurse, who will provide written and verbal information and obtain informed consent to participate following standardised procedures [27]. We aim to recruit 40 parents.

Recruitment of healthcare professionals: Healthcare professionals (*n* ~ 10–15 medical, nursing, and allied health staff) involved in the care of children with cancer will be recruited through professional networks.

Study inclusion and exclusion criteria are presented in Table 3.

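### Professionals who co-designed RECOVER may be among the 10–15 who report on it, and their answers are not separated; this sets a floor under the awareness percentage in Table 4

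*Protocol article*

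**What the plan says.** **Who designed the model.** Table 1 heads its first block "Healthcare Professionals *n* = 22" and splits it into 10 nursing, 8 allied health and 4 medical. Section 2 (Participants and setting) says of them: "They were recruited from the Queensland Children’s Hospital and included representation across medical, nursing and allied health specialists". It adds how they were chosen: "Healthcare providers were selected based on their involvement in patient care and ability to provide valuable insights".

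**Who evaluates it.** Section 2.5 states: "Healthcare professionals (*n* ~ 10–15 medical, nursing, and allied health staff) involved in the care of children with cancer will be recruited through professional networks". Table 3 admits "Clinicians (doctors, nurses, and allied health professionals) who provide care through Queensland Health public hospitals; The participants’ nominated family general practitioner" and gives the exclusion as "None; all clinicians who meet the inclusion criteria are eligible to participate".

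**What they report.** Sections 2.6 and 2.7 ask professionals, including the family's general practitioner, about acceptability, satisfaction, relevance to practice, barriers and enablers. Table 4 adds, under adoption and maintenance, a percentage of professionals who are aware of the model.

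**What is conceded.** Section 3.4 names as a limitation the voluntary participation of parents and professionals "whose decision to participate may be influenced by their interest or personal commitment to the project". It does not mention overlap with the design group.

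**The concern.** Someone who helped build a model of care is not in the same position as a clinician who meets it for the first time. Table 3 puts both in one sample, and the article describes no step that tells them apart afterwards.

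This has two consequences. First, awareness among co-designers is certain, so counting them in an adoption measure partly measures who took part in the design. Second, Section 2 says that stakeholder feedback was built in so that the finished model would be acceptable to providers. Asking the same people whether it is acceptable partly repeats that exercise. It says less about clinicians who would have to take the model up in routine practice.

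**Working it through.** **1. Reproduce the count.** From Table 1: 10 + 8 + 4 = 22, as stated.

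**2. Compare with the places.** Section 2.5 plans n of about 10 to 15.
- Ratio: 22/15 = 1.5 and 22/10 = 2.2.
- Respondents from outside co-design that the rules require: max(0, n − 22) = 0 for both n = 10 and n = 15.
- Table 1 includes general practitioners in its medical group, so some of those 4 may not be hospital staff. Setting all 4 aside leaves 18, still enough for 15 places.

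The permitted share of co-designers is therefore 0 to 100%.

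**3. What mix is plausible?** The article does not give the number of eligible clinicians, N. Assume values for N and, for orientation only, a random draw. The expected share is 22/N, P(at least one) = 1 − C(N−22, n)/C(N, n), and P(all) = C(22, n)/C(N, n).

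| Assumed N | Expected share | P(at least one), n = 10 / 15 | P(all), n = 10 / 15 |
|---|---|---|---|
| 22 | 100% | 100% / 100% | 100% / 100% |
| 30 | 73% | 100% / 100% | 2.2% / 0.1% |
| 40 | 55% | >99.9% / >99.9% | 0.08% / <0.01% |
| 60 | 37% | 99.4% / >99.9% | <0.01% / <0.01% |
| 100 | 22% | 92.7% / 98.3% | <0.01% / <0.01% |

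Some overlap is very likely over this range, while a sample made up only of co-designers is unlikely once N reaches 30. Recruitment through professional networks is not a random draw, so the table shows orders of magnitude and is not a forecast.

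**4. Effect on the awareness percentage.** Let s be the share of co-designers and a the awareness among other professionals. Co-designers have awareness 1, so

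observed awareness = s × 1 + (1 − s) × a ≥ s,

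and the excess over awareness in other staff is s(1 − a). The floor is s itself: 25%, 50% or 75% with a quarter, half or three quarters co-designers. At the expected shares above for N = 30 to 100, it is 73% down to 22%. This needs no assumption about attitudes, only that the percentage is taken from this sample and that co-designers know the model.

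**5. Effect on satisfaction and relevance.** The article sets no satisfaction percentage or threshold for professionals, and Section 2.9.1 assigns interview and free-text data to thematic analysis. It gives no satisfaction rates for either group, so no figure can be put on this part.

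**The case against.** A reader might infer that acceptability, a primary objective, will be judged by the model's own designers. The documents do not support that. Section 2.7 also assesses acceptability in parents, through interviews and a survey-completion rate of at least 70%. That rate is the only numerical acceptability criterion, and it concerns parents alone.

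Nor do the documents support the idea that all professional respondents will be co-designers. Step 3 shows this to be the permitted extreme. Section 2.7 and Table 3 also bring in family general practitioners nominated by participants, and few of these can have been co-designers, since Table 1 has only 4 medical professionals across several specialties. Whether these practitioners count within the 10–15 is not stated. Nothing in the article shows that professional networks reach co-designers first, and Table 3 opens eligibility to clinicians across Queensland Health public hospitals.

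Upward bias in ratings is not established either. Table 2 records stakeholders doubting whether the model was feasible in practice. At a single centre, co-designers are also end-users and may be the best informants on barriers, so excluding them or giving them last call on places would be a debatable trade-off.

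It can also be said that a journal article leaves interview sampling and reporting detail to the full protocol. That is fair for detail. But Table 3 states the eligibility rule outright, and Section 3.4 discloses only a general volunteer effect. What stands is that the two groups may be mixed and that awareness is raised arithmetically when they are.

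**Conclusion.** The point holds for the professional strand. Any share of the 10–15 respondents may be co-designers, and the article does not separate their answers. That share is a floor under the awareness percentage in Table 4: at least 50% if half are co-designers, and 22% to 73% at the expected shares for assumed pools of 100 down to 30 clinicians. Favourable satisfaction and relevance ratings are possible, but their size cannot be derived from the documents. The parent results are not affected.

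This rests on three assumptions: that awareness is measured in the Section 2.5 sample, that co-designers know the model, and that Queensland Children's Hospital falls within Table 3's Queensland Health public hospitals, which the setting implies but the article does not state outright. It is an inexpensive improvement to make, and it does not call the primary objective into question.

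**What to change.** Add one question for each professional participant: did they take part in the co-design or user testing of RECOVER? Then:
- report awareness, satisfaction and acceptability separately for those who did and did not, with the number in each group;
- take the Table 4 awareness percentage from those who did not, with its denominator;
- keep co-designers eligible and retain their views on barriers and enablers;
- add the overlap to the limitations in Section 3.4.

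Table 4 schedules the professional data for the completion of data collection or of the study, so the role can still be recorded if recruitment has begun.

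The cost is the screening question and smaller subgroups. If half of 10 respondents are co-designers, 5 remain for the awareness figure and each counts for 1/5 = 20 percentage points, against 1/10 = 10 points in the full sample. The result should therefore be given as a count as well as a percentage.
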